## Abstract

To maintain the balance, the postural system needs to integrate the three main sensorial systems: visual, vestibular, and somatosensory to keep postural control within the limits of stabilization. Damage of one of these systems, in this case, the vision, will have a great disturbance on the postural control influencing the behavior of the balance, resulting in falls. The aim of this study protocol for a randomized, controlled clinical trial is to analyze the effects of transcranial direct current stimulation (tDCS) combined with proprioceptive exercises on postural control in individuals with congenital and acquired blindness. In this randomized, controlled, double-blind, clinical trial, male, and female individuals with blindness between 18 and 55 years of age will participate in this study divided into three phases: 1—Determine differences in postural control and gait between individuals with congenital and acquired blindness with and without the use of a guide stick when wearing shoes and when barefoot; 2—A pilot study to analyze the effects a bilateral cerebellar anodal tDCS on postural on postural control and gait; and 3—A treatment protocol will be conducted in which the participants will be allocated to four groups: G1—active tDCS + dynamic proprioceptive exercises; G2—sham tDCS + dynamic proprioceptive exercises; G3—active tDCS + static proprioceptive exercises; and G4—sham tDCS + static proprioceptive exercises. Evaluations will involve a camera system for three-dimensional gait analysis, a force plate, and electromyography. Dynamic stability will be determined using the Timed Up and Go test and static stability will be analyzed with the aid of the force plate. The viability of this study will allow the determination of differences in postural control between individuals with congenital and acquired blindness, the analysis of the effect of tDCS on postural control, and the establishment of a rehabilitation protocol.

## Introduction

Postural control (PC) can be negatively affected in individuals with blindness due to the lack of availability of visual input (1, 2). The proprioceptive system cannot completely compensate this poor balance for a lack of vision even on high demand for physical activity such as sports participation (3, 4). Contributing factors in blind subjects include a lack of adequate information on the surrounding environment, spatial localization, and the orientation of body parts, which serve as a reference for perception and action in relation to the outside world (2).

Balance training or postural perturbation training, enhance proxies of static and dynamic steady-state, reactive balance, and dynamic reflex responses that induce disturbances in the sensory feedback system (5) to generate an automatic response in the neuromuscular control of a given joint. These interventions attempts to enhance PC and balance to improve the stability of the body, thereby reducing the risk of falls. A suggestion is that the central nervous system stimulates the dynamic behavior of the motor system for planning, control, and learning, integrating afferent and efferent sensory inputs during a proprioceptive activity in the absence of sight (6). Therefore, therapies that directly affect the higher centers of the central nervous system, in case of the motor cortical areas could lead to more effective results, and, transcranial direct current stimulation (tDCS) could be a way to achieve such neural changes directly.

Studies reported positive clinical effects with the use of tDCS combined with rehabilitation programs. In a meta-analysis (7) tDCS improved PC through the modulation of cortical excitability, which this technique could be a choice to enhance functionality and independence, and thus, reduce the rate of falls in individuals with a balance disorder, mainly on primary motor cortex (M1) stimulation. However, the effects of tDCS on the cerebellar cortex should be better investigated due to divergence in the study results. Are recognized that both early and late blind people have morphological changes in their whole brain, and the cerebellum is one of these structures. For example, Kosif et al. (8) showed a smaller volume of cerebellar area in congenital blindness subjects compared to sighted subjects. But systematic review studies showed positive effects of cerebellar tDCS to modulate cerebellocerebral networks (9, 10). But until the present, no study has investigated the effects of cerebellar tDCS on gait and PC in blind people.

As stated earlier for the visually impaired people, motor control is quite challenged even in simple tasks that require PC due to their blindness, and that tDCS induces cerebellar excitability changes (11), in which can modulate cerebellar-motor cortex excitability and thus, affect positively PC processing (12). The present study hypothesizes that tDCS can potentiate the effects of a proprioceptive exercises on both static and dynamic PC in blind subjects. The secondary objectives are (1) to determine possible differences in PC betweenindividuals with congenital and acquired blindness; (2) to evaluate the motor pattern of gait with and without the use of a guide stick when wearing shoes or while barefoot; and (3) to analyze whether proprioceptive exercises with or without tDCS can lead to different results with regard to PC.

## Materials and Methods

### Study Design

This study protocol is divided into three phases where phase 1 is a cross-sectional study to determine differences in postural control and gait between groups; phase 2 is a pilot study of phase three, a randomized, controlled, double-blind, clinical trial with blind individuals.

### Ethical Approval and Consent to Participate

All procedures were performed following the Guidelines and Regulating Norms of Research involving human beings, formulated by the Brazilian National Health Council—Health Ministry of Brazil, established in 2012. This study received approval from the Human Research Ethics Committee of the Nove de Julho Educational Association (No. 1.672.635/2016). The study protocol was registered in the Clinical Trial Registration (number NCT03173105). All participants and/or their person in charge must agree to take part in the study by signing an Informed Consent Form. In addition, any personal data as well as the participants' identities, based on the ethical principles of confidentiality and privacy, will be guaranteed absolute secrecy. Sham intervention procedures will always be performed in association with an active treatment, which makes its use of less impact to the patient.

### Sample and Recruitment

Preselected individuals will undergo a general assessment, with personal information, and anthropometric measurements which will be kept confidentiality under the responsibility of the researcher for the study.

The study will be conducted in three phases: (1) to determine differences in PC and gait between individuals with congenital and acquired blindness, and with/without a guide stick when wearing shoes and while barefoot compared to sighted people; (2) a pilot study to observe the effects of a cerebellar anodal tDCS on PC and gait during a proprioceptive exercises protocol; and (3) the exercise protocol with sample size calculation from phase 2. Figure 1 displays the flowchart of the proposed study process.

**Figure 1 F1:**
[figure not shown]
Flowchart of the study design. AtDCS, active transcranial direct current stimulation; StDCS, *sham* transcranial direct current stimulation; Dyn proprio, dynamic proprioception; Stb proprio, static proprioception.

Volunteers will be recruited from the community and associations that offer assistance to individuals with visual impairment. Letters will also be sent to specialized healthcare professionals to divulge the project. Some strategies will be employed to increase participation besides decreasing the dropout rate and achieve adequate participants to reach target sample size.

The characterization of congenital and acquired blindness will be based on the classification of the degree of visual impairment proposed by the World Health Organization, the International Statistical Classification of Disease and the 10th Edition of the International Classification of Disease, in which visual acuity <20/400 or <20/200 in the better eye is classified as blindness. The time schedule for trial enrollment, interventions, assessments, and participant visits is provided in Figure 2.

**Figure 2 F2:**
[figure not shown]
Schedule of enrollment, assessments, and interventions for participants.

### Eligibility Criteria

Inclusion criteria will be abnormalities of the optic nerve, retina disorders, glaucoma, Stargardt disease, macular degeneration, retinitis pigmentosa, congenital toxoplasmosis, congenital cataracts, congenital Leber's amaurosis, detached retina, and astrocytoma. For exclusion criteria: medical diagnosis of an injury, surgery, or clinical condition that can affect balance and gait; the use of medication affecting the central nervous system, coordination or balance; current symptoms of vertigo or dizziness. Additional exclusion criteria that should be considered for tDCS are: frequent migraines/headaches, scalp or skin conditions, metallic implants within the body, and seizures.

### Evaluation Procedures

All evaluations will be done at baseline and post-immediately therapeutic intervention, Also in 1 and 3 months as follow-ups (Figure 1).

#### Three-Dimensional Gait Analysis

Gait will be analyzed on a track measuring 90 centimeters in width and five meters in length. The SMART-D 140 system (BTS Engineering, Milan, Italy) will be used, which has eight infrared light-sensitive cameras and synchronized to a video system and computer containing the SMART-D INTEGRATED WORKSTATION® with 32 analog channels. Two force-platforms (Kistler, model 9286BA) will be used for the collection of kinematic gait data, the recording of the displacement of the center of pressure and the contact time between the foot and the surface of the force-platform. To ensure consistency in the results, at least six steps will be performed during each evaluation. The following indices will be analyzed based on the kinematic, kinetic: spatiotemporal variables (velocity, cadence, step length, stride length, stance phase, and swing face) and joint angles at specific moments of gait (pelvis inclination, hip flexion-extension, knee flexion-extension, and ankle dorsiflexion-plantar flexion) as well foot progression.

#### Surface Electromyography (sEMG) Activity

The sEMG (BTS Engineering, Milan, Italy) analysis of the right tibialis anterior, lateral gastrocnemius, rectus femoris, biceps femoris, rectus abdominal, lumbar paravertebral, sternocleidomastoids, and upper trapezius muscles will be performed, with a bioelectric signal amplifier, wireless data transmission and bipolar electrodes with a total gain of 2,000 within a frequency of 20–450 Hz. The impedance and the common rejection mode ratio of the equipment are >1,015 Ω//0.2 pF and 60/10 Hz 92 dB, respectively. All electromyographic data will be captured and digitized in 1,000 frames/second software program (BTS MYOLAB, Milan, Italy) and collected simultaneously to the kinematic and kinetic data.

#### Timed Up and Go (TUG) Test

The participants will be instructed to perform the test at a safe, self-selected pace. Blind subjects will be guided under the voice command of the researcher signaling the moment to turn around, and then to return to a seated position in the chair. Velcro strips were attached to the wall ~12–18 inches from the chair to serve as a “prompt” that the chair was nearby. The participants will be instructed to perform this task at a safe pace but were told that their time was recorded (13). The TUG test will be performed with shoes and barefoot with and without a guide stick.

#### Stabilometry

The acquisition frequency of the force-platform will be 50 Hz, captured by four piezoelectric sensors measuring 400/600 mm positioned at the extremities of each force-platform (BTS Infinity-T, Milan, Italy). The data will be recorded and interpreted using the SWAY software program (BTS 161 Engineering) integrated and synchronized to the SMART-D 140 system (BTS MYOLAB, Milan, Italy). The participants will be instructed to remain in a quiet standing position with arms alongside the body and head held in the vertical position. Three measurements (45 s each) will be performed to collect postural balance of COP (95% confidence ellipse area; velocity, and RMS in anteroposterior and mediolateral directions), and COP–COG in each condition (hard and soft surface).

### Intervention Procedure

tDCS (Trans-Cranial Technologies, USA) will be administered simultaneously during the proprioceptive exercises, ~20 min by specialized physical therapist, with two non-metallic sponge (5 × 7 cm^2^) moistened with a saline solution (15–140 mM). Anodal tDCS will be administered over the cerebellum positioned centrally located 1.5 cm below the inion, and the cathode electrode will be positioned centrally on the forehead (over Cz) (14). A current of 2 mA (0.06 mA/cm^2^) will be used during each proprioceptive exercise session. For sham tDCS, the electrodes will be positioned as described, but the stimulator will be switched on only for the first 30 s, giving the participant the initial sensation of tDCS, but without active stimulation throughout the remainder of the session.

#### Adverse Effects

The adverse effects of tDCS will be evaluated at the end of each session using a questionnaire addressing the perception of symptoms that might occur during the session, such as tingling, burning sensations, headache, pain at the electrode sites, drowsiness, and mood alterations.

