#### Proprioceptive Exercises

The intervention will be divided into static and dynamic proprioceptive exercises. The static exercises will be conducted as follows: (1) standing on the toes with the feet apart; (2) standing on the toes with the feet together; (3) standing on only the right leg without support; (4) standing on only the left leg without support; and (5) standing with the heel of the right (or left) foot touching the toes of the left (or right) foot with the feet in a straight line (tandem). Exercises will be performed on an unstable surface (wobble board) on the anteroposterior (three sets) and laterolateral (three sets) axes. Each exercise will be performed in six sets of 30 s each, with a 1-min rest between sets. For dynamic proprioceptive exercises: (1) walking slowly then more quickly on a trampoline; (2) walking backward with one foot behind the other; (3) walking forward on a beam; (4) going up and down a flight of stairs; and (5) sitting on a Swiss exercise ball (65 cm) and performing laterolateral and anteroposterior movements, circling movements and bouncing. Activities 1–4 will be performed in three 1-min sets, and activity five will be performed in sets with 30 s of each movement. Throughout all exercises, a physical therapist will remain beside the participant to avoid excessive imbalance and the risk of falls.

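### The harms rule is tied to tDCS symptoms felt within a session; the article states no recording of falls, of events between sessions, or of events up to the 3-month visit

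*Protocol article*

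**What the plan says.** Under Adverse Effects, the protocol article states one rule for the unwanted effects of stimulation, namely that they "will be evaluated at the end of each session using a questionnaire addressing the perception of symptoms that might occur during the session". It then gives examples: "such as tingling, burning sensations, headache, pain at the electrode sites, drowsiness, and mood alterations".

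Under Evaluation Procedures it schedules the assessments: "All evaluations will be done at baseline and post-immediately therapeutic intervention, Also in 1 and 3 months as follow-ups". The measurements described there are three-dimensional gait analysis, surface EMG, the Timed Up and Go test and stabilometry.

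Under Proprioceptive Exercises, participants work on a wobble board, trampoline, beam and stairs, and "a physical therapist will remain beside the participant to avoid excessive imbalance and the risk of falls". Under Eligibility Criteria, people with "current symptoms of vertigo or dizziness" are excluded at entry.

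The Abstract and Introduction name falls as a consequence of poor postural control and as something that balance training and tDCS might reduce.

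**The concern.** The article does more than leave harms to another document. It states a rule, and the rule is narrow in three ways: tDCS effects, asked at session end, about that session. Staff who followed it would not ask about the days since the last session, and would have no instruction to log a fall or a therapist's catch, since neither is a perceived symptom of stimulation.

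Two things are at stake. First, a low count of falls or delayed events could reflect how the question was asked rather than what happened, and a reader could take it as evidence of safety. The Introduction says that cerebellar tDCS has not been studied for gait and postural control in blind people, so the trial's own harms data matter. Second, collection limited to tDCS effects asks someone to attribute the event before it is recorded. A sham-controlled comparison does not need that step. It also leaves the exercise factor, where static and dynamic programmes could plausibly differ in falls, without a stated harms rule.

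**Working it through.** The plan gives no figure on harms and no event rate, so there is nothing to recompute. The check sets each type of event against the places where the article could collect it.

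| Event | Stated collection point | Basis |
|---|---|---|
| tDCS symptom felt during a session | Yes, session-end questionnaire | Adverse Effects |
| Dizziness felt during a session | Not named, but not excluded | Adverse Effects: the list gives examples only |
| Fall, near-fall or therapist catch during exercise | None stated | Proprioceptive Exercises describes prevention, not recording |
| Event starting after a session, before the next | None stated | The next questionnaire again covers only its own session |
| Event from the last session to 3 months | None stated | Evaluation Procedures describes gait, EMG, Timed Up and Go and stabilometry only |

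Three observations follow.

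1. **Recall window.** Because each questionnaire looks back only over its own session, successive questionnaires do not join up. A headache or skin reaction that begins that evening is outside the window of both the session before and the session after.

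2. **Randomised factors.** Randomization crosses active or sham tDCS with dynamic or static exercise, giving 2 × 2 = 4 groups. The harms rule covers effects of tDCS, so 1 of the 2 factors has a stated rule.

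3. **Visits.** Evaluations are at baseline, immediately after the intervention, and at 1 and 3 months, so 4 − 1 = 3 follow baseline. The questionnaire sits under Intervention Procedure and is tied to sessions; nothing shown carries it to any of these 3 evaluations. The contacts already exist ("Also in 1 and 3 months as follow-ups"), so asking there needs no new visit.

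The Statistical Analysis section lists gait, center-of-pressure and EMG variables as dependent variables. The absence of a harms variable there is not counted as a fault, since a harms table may sit in a fuller plan. It means only that this section does not widen the stated rule.

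**The case against.** The strongest reply is that this is a condensed article. Reporting of events between visits and of serious events commonly sits in the full protocol. The section describes one tolerability questionnaire and does not say that nothing else is recorded. The schedule in Figure 2 is not visible in the text reviewed. Falls are background and a supervised hazard, not an outcome: Sample Size Estimation names gait speed and displacement of the center of pressure.

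Much of this stands. It rules out several stronger readings that a reader might be tempted to make:

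- **That falls and delayed events are recorded nowhere.** The documents show only that no such recording is stated in the article.
- **That dizziness is left out.** The symptom list is illustrative, so dizziness during a session is within scope. Only dizziness that starts later is outside the stated window.
- **That every entry exclusion should appear as a harm item.** Eligibility criteria are not a harms list, and headache, which is also an exclusion, does appear among the examples.
- **That coverage is only the stimulation time.** The question covers the session. The static programme alone, as written, is 5 exercises × 6 sets × (0.5 + 1) min = 45 min if a rest follows every set, against about 20 min of tDCS.
- **That a number of missed fallers can be given.** The documents contain no fall rate.

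What the reply does not remove is the rule itself. Its object, timing and window are written out, and following it misses the events in the last three rows of the table. If fuller collection exists elsewhere, this section is narrower than the trial's actual practice and the two need to agree.

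**Conclusion.** The point holds as a worthwhile, inexpensive improvement to a rule that the article has drawn too narrowly. It is not an error that alters an efficacy estimate, a test or a primary outcome. The stated rule covers tDCS symptoms within a session. It does not reach falls or near-falls in the exercises, events between sessions, or events up to the 3-month visit. The size is the gap in coverage shown above; it cannot be turned into a number of events.

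The conclusion assumes that the text shown is what staff would follow. It would reduce to a matter of reconciling documents if the full protocol or Figure 2 provides wider collection. A reader might also infer that unrecorded dizziness from cerebellar stimulation would explain a worse result on gait speed or center of pressure. That is possible, but no passage says that such dizziness is expected, so the point does not rest on it.

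**What to change.** Keep the end-of-session questionnaire and add to the Adverse Effects section:

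- A short checklist of events since the last contact, asked at the start of each session and at the existing post-intervention, 1-month and 3-month evaluations.
- Named items for falls, near-falls (including any catch by the therapist during exercise), dizziness or vertigo, and skin reaction.
- Recording of each event whether or not it is attributed to tDCS.
- A descriptive report of the number of participants with at least one event, by active versus sham and by static versus dynamic. In Phase II, with 10 per group, each margin has 2 × 10 = 20 participants, so no formal comparison should be made.

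If the full protocol or Figure 2 already provides for any of this, align the Adverse Effects section with it instead.

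The cost is a few minutes per visit, one more case-report page and one table, with no added visits or staff. The drawback is recall error: over intervals of 1 to 3 months, participants will forget or misdate some falls, so the follow-up counts should be described as recalled events.

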#### Proprioceptive Exercises

The intervention will be divided into static and dynamic proprioceptive exercises. The static exercises will be conducted as follows: (1) standing on the toes with the feet apart; (2) standing on the toes with the feet together; (3) standing on only the right leg without support; (4) standing on only the left leg without support; and (5) standing with the heel of the right (or left) foot touching the toes of the left (or right) foot with the feet in a straight line (tandem). Exercises will be performed on an unstable surface (wobble board) on the anteroposterior (three sets) and laterolateral (three sets) axes. Each exercise will be performed in six sets of 30 s each, with a 1-min rest between sets. For dynamic proprioceptive exercises: (1) walking slowly then more quickly on a trampoline; (2) walking backward with one foot behind the other; (3) walking forward on a beam; (4) going up and down a flight of stairs; and (5) sitting on a Swiss exercise ball (65 cm) and performing laterolateral and anteroposterior movements, circling movements and bouncing. Activities 1–4 will be performed in three 1-min sets, and activity five will be performed in sets with 30 s of each movement. Throughout all exercises, a physical therapist will remain beside the participant to avoid excessive imbalance and the risk of falls.

